### Data management and analysis

Data will be exported from the MOXXI system and analyzed using SAS software (Cary, NC, USA). All data analysis will be performed in secure physical locations using hardware that is password protected. Only study personnel will have access to the data. Simple descriptive statistics to describe the patient population, call statistics and outcome measures will be used. Continuous variables will be described using median and inter-quartile ranges, while categorical variables will be described using frequency distributions. The statistical significance of any associations between group assignment and measures will be assessed using the Wilcoxon rank sum test and or the chi-square test, respectively, for continuous and categorical variables. Since the primary outcome is binary, tests to compare outcomes between the intervention and control groups will be simple chi-square statistics. An alpha of 0.05 as a threshold to determine statistical significance using a two-tailed distribution will be applied.

As a sensitivity analysis, logistic regression modeling will be used to assess possible baseline factors that are associated with the outcome and differ between the intervention and control groups. Analogous analyses to assess significance for the individual components of the composite primary outcome and the binary secondary outcome variables will also be performed (ADE occurrence, preventable ADE occurrence and ameliorable ADE occurrence).

To compare health services utilization, since the outcomes are event data, which follow a Poisson distribution, incidence rates for the outcome will be calculated. Incidence rates will be calculated using PROC GENMOD to create a *t*-test. Multivariable Poisson regression will be used to compare the rates, while adjusting for baseline factors. The model will use the treatment group as an independent covariate. If over-dispersion is noted, a negative binomial model will be used.

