### Randomization

The unit of analysis for the study is the individual patient, each of whom we will randomly assign to the intervention or control arms using a computer algorithm. We will perform stratified randomization at the physician practice level with block sizes of four. We will only randomize patients once a physician confirms the patient’s eligibility for enrolment. We will update the ISTOP-ADE system with the patient’s treatment group but this information will not be available to the prescribing physician or the patient.

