#### Explanatory variables

To determine factors that influence outcomes, we will use data in the MOXXI system to derive baseline information on patients, including demographic information (age, gender, language of choice and location of residence), active and past medical diagnoses and medication use in the preceding year (number of new drug starts and adherence).

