### Sample size

We have based our sample size on the following assumptions:A baseline probability of non-persistence of 25% (based on a prior research study evaluating persistence with anti-hypertensive therapy using the same methods we will for this study) [11]A minimally clinical important difference of 20%A 10% loss to follow-up (based on our pilot study)An enrollment rate of 50% (based on our pilot study)Other specifications: α = 0.05, β = 0.20 and two-sided tests for significance will be used

Given these assumptions, we will need to approach 4,708 patients in total (2,354 patients in each treatment arm being eligible and approached for enrollment). This will result in 2,354 patients being enrolled (1,177 patients in each arm) and 2,118 patients evaluated for the composite outcome (1,059 patients in each arm). To be more conservative, we will enroll 1,100 patients in each arm.

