This is an ambitious study, which will run in over 100 primary care practices in two large urban settings. It will take 3 years to complete the recruitment and follow-up. We are randomizing patients at the patient rather than provider level because there is little risk of contamination or co-intervention. The patients are unlikely to interact with each other, and, based on our pilot study, there was very little interaction between patients and doctors within the 3 weeks of their prescription. There are some sources of bias in our design to be considered. The primary risk is the lack of blinding in patients and primary care doctors. This is a concern as knowledge of allocation could change behavior. However, based on findings from our pilot study, we predict this is unlikely. In addition, outcome assessment is done objectively or by blinded reviewers. In short, this study will have internal validity and will be generalizable.

In summary, we have previously developed an automated outreach program for patients prescribed new medications. We have tested this intervention in a pilot study. This work found the intervention to be feasible and suggested it might improve the quality of patient care through reduced ADE duration and improved medication adherence. We have designed this randomized trial to test whether the intervention is effective compared to routine care. If the ISTOP-ADE system were demonstrated to be effective, then there would be significant opportunities to implement this intervention through health systems, health insurance agents and commercial pharmacies.

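### The chi-square for the primary and binary secondary outcomes leaves out the practice strata used in randomisation, and their only adjusted model picks covariates by observed imbalance: valid, but inefficient and not fixed in advance

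*Protocol article*

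**What the plan says.** The Randomization section of the protocol article assigns individual patients and states: "We will perform stratified randomization at the physician practice level with block sizes of four". The Discussion describes a study "which will run in over 100 primary care practices in two large urban settings", so there are many strata.

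Under Data management and analysis, the primary outcome is treated as binary and "tests to compare outcomes between the intervention and control groups will be simple chi-square statistics". The ADE, preventable ADE and ameliorable ADE outcomes are to be handled in the same way. Practice is not mentioned in that section.

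The adjusted analysis of the primary outcome is a logistic regression, labelled a sensitivity analysis. It is to assess possible "baseline factors that are associated with the outcome and differ between the intervention and control groups".

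The Explanatory variables section lists what the MOXXI record will supply: demographics, diagnoses and "medication use in the preceding year (number of new drug starts and adherence"). It does not say which of these enter a model.

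**The concern.** Two choices do not fit the design.

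First, small blocks within practice force the arms to be nearly balanced on practice. Differences between practices therefore contribute almost nothing to the real variability of the treatment comparison. A simple chi-square still counts those differences as random error. If persistence varies by practice, its standard error is too large and some power is lost.

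Second, the logistic model admits a factor when it is associated with the outcome and differs between arms. After randomisation, between-arm differences in baseline factors arise by chance. Both criteria are judged on the observed data and one of them uses the outcome, so nobody can say in advance which model will be fitted. A factor that predicts persistence well but happens to be balanced would be left out, although adjusting for it would still add precision. A model built this way is also weak evidence for or against the primary result.

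At stake are precision and pre-specification, not false positive findings.

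**Working it through.** **Inputs from the Sample size section.** Control non-persistence 25%; "A minimally clinical important difference of 20"%; two-sided alpha 0.05; power 80%; 10% loss to follow-up; 1,059 evaluable per arm; 1,100 enrolled per arm. The 20% must be relative (25% against 20%), because an absolute 20 points (25% against 5%) would need only 49 per arm.

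**Assumptions, with no figure in the article.** The ICC of persistence between practices (0 to 0.20 on the latent logistic scale), and the share of outcome variance, R², explained by practice plus baseline covariates (5% to 10%).

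**Step 1: the plan's own figure.** With mean risk 0.225,

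n = [(1.960 × √(2 × 0.225 × 0.775) + 0.842 × √(0.25 × 0.75 + 0.20 × 0.80)) / 0.05]² = 1,094 per arm.

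The unpooled version gives 1,091 and the arcsine version 1,092. The stated 1,059 is a little lower and gives 78.7% power. This gap is a separate matter and the present point does not depend on it.

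**Step 2: power of the planned test.** The enrolment target leaves 1,100 × 0.9 = 990 evaluable per arm.

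Power = Φ[(0.05 × √990 − 1.960 × √0.34875) / √0.3475] = Φ(0.705) = 76.0%.

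**Step 3: cost of ignoring practice alone.** Simulation used 6,000 trials per setting, 1,980 evaluable patients, 100 practices of unequal size (about 20 patients each) and blocks of four within practice. The simple chi-square was compared with a practice-stratified Cochran-Mantel-Haenszel (CMH) test, which stands in here for any analysis that respects the strata.

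| Assumed ICC | Power, chi-square | Power, CMH | Type I error, chi-square | Type I error, CMH |
|---|---|---|---|---|
| 0 | 76.1% | 75.8% | 5.0% | 5.2% |
| 0.02 | 76.4% | 76.4% | 5.1% | 5.3% |
| 0.05 | 76.4% | 77.0% | 4.7% | 4.7% |
| 0.10 | 76.7% | 78.2% | 3.9% | 4.7% |
| 0.20 | 77.8% | 81.5% | 3.6% | 4.9% |

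Monte Carlo standard errors are about 0.5 points for power and 0.3 points for type I error. The chi-square never exceeds its nominal level by more than simulation error. It becomes clearly conservative only from an ICC of about 0.10.

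**Step 4: adding baseline covariates.** As an approximation, adjustment acts like a sample of n / (1 − R²):

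- R² = 5%: 990 / 0.95 = 1,042 per arm, power 78.1%.
- R² = 10%: 990 / 0.90 = 1,100 per arm, power 80.2%.

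This R² covers practice and covariates together, so the gain must not be added to that of Step 3.

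**The case against.** The strongest reply is that an unadjusted chi-square, fixed in advance, is a legitimate primary analysis for an individually randomised binary outcome. That stands. A reader might infer that ignoring the strata inflates the false positive rate or makes the primary p-value depend on the data. The simulation shows the opposite direction for the first. For the second, data-driven selection affects only the sensitivity model.

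It is also fair that the loss from the strata alone is within or close to simulation error up to an ICC of 0.05, and that the article gives no ICC. The larger losses need practices to differ substantially.

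A reader might take the listed baseline variables to be strong predictors of persistence. The article does not say so. Because the index drug must be new to the patient, prior-year adherence can only concern other drugs. The R² of 5% to 10% is therefore illustrative.

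A reader might also conclude that the plan has no other adjusted model. It does, for health services utilization: "Multivariable Poisson regression will be used to compare the rates, while adjusting for baseline factors", with no imbalance criterion. The criticism is confined to the binary outcomes.

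The article sets no selection threshold or algorithm for the logistic model, and a full covariate list may properly sit in an analysis plan not shown here. The missing list is not the finding. The finding is the criterion that the article does state, which points to selection by observed between-arm difference.

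Finally, power below 80% at 990 per arm comes from the enrolment target and should be judged separately. It sets the starting point for the arithmetic but is not evidence for this point.

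**Conclusion.** The point holds as one of efficiency and pre-specification. The planned test for the primary and binary secondary outcomes does not reflect the stratified randomisation. It is valid, and conservative when practices differ: at an assumed ICC of 0.10 to 0.20 its actual type I error is 3.9% to 3.6%.

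The power lost by ignoring practice is about 0 to 0.6 points at an ICC up to 0.05, 1.5 points at 0.10 and 3.7 points at 0.20. With baseline covariates as well, the gain at 990 per arm would be about 2 to 4 points if the assumed R² of 5% to 10% were right. Direction and mechanism are secure; size is not, because neither the ICC nor the R² has a source in the article.

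The covariate rule in the sensitivity model is poor practice whatever these values are. The change is worth making because it costs almost nothing. It does not repair a biased or invalid primary analysis, because the planned one is neither.

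**What to change.** Make the primary analysis one pre-specified logistic model with treatment, practice as a random intercept, and a short fixed list of baseline covariates. Candidates are age, sex, index condition, prior-year adherence to other drugs and number of new drug starts. Name the list before outcome data are seen, and state how patients with no other drug in the prior year are coded for adherence. Report a standardised risk difference with 95% CI, since the model's odds ratio is conditional on practice and covariates.

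Use the same model for the binary ADE outcomes. Keep the simple chi-square, or a practice-stratified CMH test, as a sensitivity analysis. CMH is not an equivalent choice for the primary analysis, because over 100 or more practices it cannot also carry the covariate list. Delete the selection of covariates by observed between-arm difference.

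The cost is new wording and slightly more analysis work, mainly programming the standardised risk difference and its interval. No extra patients are needed, and the covariates come from the MOXXI record. The Trial status section places the start of the study in the future, so as the article stands the change can precede any outcome data.

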### Ethical considerations

The physicians and their patients enrolled in the MOXXI program are covered under an umbrella consent program, which is approved and monitored by McGill’s Institutional Review Board. In addition, patients will be given opportunities to become informed about the project and to withdraw, as appropriately defined under the Tri-Council’s guidelines.

### Timeline

The entire ISTOP-ADE study will take 5 years from start to finish. Patient enrolment will run for 3 years to ensure sample size requirements are met. Patient follow-up will continue for 1 year from enrolment. Case summaries and physician reviews, as well as data validation and quality checks will occur throughout the lifespan of the study. We have budgeted 12 months to accomplish the analysis and knowledge translation activities.

## Discussion

We have planned this randomized trial to assess the effectiveness and cost-effectiveness of an automated outreach program to monitor patients receiving a new ambulatory care prescription. It is an important study as the intervention has shown promising results in a pilot study. Some health payers and pharmacies may feel that this intervention is already warranted on face value and based on our preliminary findings. We have advised against this approach as the system has not been compared against routine care. In a situation where there are limited resources, it is not appropriate to invest in interventions of unknown effectiveness.

We chose adherence with prognosis-altering medications as our primary outcome. This outcome is important as many studies have demonstrated poor adherence – approximately 50% of patients with chronic illness do not take their medication as prescribed – and this in turn has been estimated to have major impacts on disease progression and health-care costs
[20, 21]. We will assess this outcome using administrative data. This ascertainment method has been demonstrated to be accurate and will not be biased by an inability to blind patients to the intervention. Our secondary outcomes are similarly important. In particular, ADEs are common following incident prescriptions
[15, 16]. While many of the symptoms related to ADEs are short in duration, a substantial proportion of patients have symptoms lasting longer than 7 days and can lead patients to discontinue their medications on their own. Collectively, these outcomes will allow us to assess adequately the value of our intervention to patients and the health-care system.

Our study will also give us an opportunity to assess further implementation issues. We will track the costs of the intervention closely, including the workload required by our pharmacist to follow up the automated calls and by the physicians, who may need to do extra work to respond to patient complaints. We will also assess the failed automated calls to assess which patients do not accept this type of intervention. Finally, we will conduct an assessment of patient factors associated with adherence. All of this information will guide decisions pertaining to whether and how this system should be implemented, and to whom it should be directed.

This is an ambitious study, which will run in over 100 primary care practices in two large urban settings. It will take 3 years to complete the recruitment and follow-up. We are randomizing patients at the patient rather than provider level because there is little risk of contamination or co-intervention. The patients are unlikely to interact with each other, and, based on our pilot study, there was very little interaction between patients and doctors within the 3 weeks of their prescription. There are some sources of bias in our design to be considered. The primary risk is the lack of blinding in patients and primary care doctors. This is a concern as knowledge of allocation could change behavior. However, based on findings from our pilot study, we predict this is unlikely. In addition, outcome assessment is done objectively or by blinded reviewers. In short, this study will have internal validity and will be generalizable.

In summary, we have previously developed an automated outreach program for patients prescribed new medications. We have tested this intervention in a pilot study. This work found the intervention to be feasible and suggested it might improve the quality of patient care through reduced ADE duration and improved medication adherence. We have designed this randomized trial to test whether the intervention is effective compared to routine care. If the ISTOP-ADE system were demonstrated to be effective, then there would be significant opportunities to implement this intervention through health systems, health insurance agents and commercial pharmacies.

## Trial status

The ISTOP-ADE study is anticipated to start early 2015.

## Abbreviations

ADE: adverse drug event
ISTOP-ADE: Information Systems-enabled Outreach for Preventing ADEs
IVRS: interactive voice response system
MOXXI: Medical Office of the 21st Century
RAMQ: Régie de l’assurance maladie du Québec.
